### Neurophysiological function

Large nerve function is assessed by electroneurography of motor and sensory nerves in the upper and lower extremities. Small nerve fiber function is assessed by a standardized quantitative sensory test including a thermal threshold test in the feet and hands. Autonomic nerve function will be tested using sympathetic skin response (SSR) and heart rate variability (HRV) testing. Needle EMG is performed in proximal and distal muscles to assess the integrity of motor units; the presence of denervation potentials, neurogenic and myogenic motor units are quantified and recorded.

**Nerve conduction studies (NCS):** All participants will have a routine NCS at the same clinical neurophysiology laboratory on the dominant lower and upper limb using the Cadwell Sierra Summit EMG system (Cadwell Industries, Inc., Kennewick, WA). Skin temperature was maintained over  $32^\circ\text{C}$ . Filters will be set

at 20 Hz–10 kHz for motor studies and 20 Hz–3 kHz for sensory studies. Motor studies included the median, ulnar, fibular, and tibial nerves, and the compound muscle action potential (CMAP), distal latency (DL), conduction velocity (CV), and minimum F-wave latency will be recorded for all nerves. Sensory studies will include median, ulnar, radial, sural, and fibular nerves, and the sensory nerve action potential (SNAP) and CV will be recorded for all nerves.

**Electromyography (EMG):** Needle-EMG of deltoid, biceps brachii, trapezius, anterior tibial, vastus medialis, and adductor magnus muscles will be performed in all participants using a concentric 35 mm needle electrode (26 G) with filter settings of 20 Hz–10 kHz. The EMG will be performed by 1–2 skin insertions per muscle at 5–10 different muscle sites separated by at least 2 mm. Quantitative EMG (qEMG) analysis will be done by sampling at least 20 motor unit potentials (MUPs) during weak voluntary contraction; gain (200 uV/division) and sweep speed (5–10 ms/division). Multi-MUP analysis and routine EMG will be performed to record and assess MUPs qualitative and semi-quantitatively. Mean duration (simple MUPs), amplitude, and percentage of polyphasic MUPs will be recorded. The presence of spontaneous activity and the interference pattern (IP) will be assessed on all tested muscles. Physician will then assess the EMG results qualitatively by visually observing clear overrepresentation of MUPs with myopathic morphology (if more than 50% of the saved MUPs data exhibited myopathic changes (short durations, small, polyphasic) together with supportive measures from the qEMG, particularly polyphasia, to classify a muscle as myopathic or not. Then the final impression/conclusion from the EMG test was classified as definitively myopathic if seen in at least 2 muscles, borderline if seen in one, neurogenic, mixed, or normal EMG findings. The Sierra Summit EMG system (Cadwell Laboratories Inc., Kennewick, WA, USA) was used for all measurements.

**Sympathetic skin response (SSR):** A standard surface electrode will be attached to the dominant palm and sole and the reference electrode to the dorsum of the hand and foot. Single electrical stimulus at the contralateral wrist (median nerve) of 20–30 mA intensity and 0.2 ms duration will be delivered. The stimulus will be delivered unexpectedly to avoid habituation. The response will be recorded, and the latency determined from the onset of the stimulus artifact to first deflection from baseline. A response will be defined as absent if no reproducible deflection is recorded after consecutive and sporadic stimulations. The Sierra Summit EMG system (Cadwell Laboratories Inc., Kennewick, WA, USA) will be used for all measurements.

**Heart rate variability (HRV):** Continuous electrocardiogram (ECG) will be recorded by a two-lead electrocardiograph using the Sierra Summit EMG system (Cadwell Laboratories Inc., Kennewick, WA, USA). The variation in R-R interval during normal breathing and during deep breathing will be recorded and the variability calculated as maximum heart rate minus minimum heart rate divided by average heart rate, expressed as a percentage.

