### Cardiovascular/circulatory/respiratory function and work capacity

Echocardiography, head-up TILT test and spirometry will be assessed according to established clinical procedures. Cardiopulmonary exercise test (CPET) to assess  $VO_{2peak}$  will be determined with an incremental cycling test to volitional fatigue on an electronically braked cycle ergometer using an online gas collection system. Arterial stiffness will also be captured through arteriography. Blood volume will be assessed using the CO-rebreathing method.

**Echocardiography:** A licensed biomedical scientist will conduct the echocardiographic examination using the Vivid E9 ultrasound system by General Electric in Horten, Norway with a 4V2c phased-array transducer. The subjects were positioned in the left lateral recumbent posture following a 5-minute supine rest, adhering to the clinical protocol derived from guidelines by the American Society of Echocardiography and the European Association of Cardiovascular Imaging. Subsequently, another blinded observer will quantify cardiac chamber dimensions and volumes, as well as the assessment of left ventricular systolic and diastolic function.

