## **17. BLINDING**

Researchers will be blinded as far as possible during data collection, in terms of group (post-COVID-19 vs. control). For example, the study personnel who conduct the clinical tests and/or exercise trials (physicians, biomedical analyst, research assistants etc.) will not be aware of the group allocation (Patient or Control). However, in some cases given the symptoms and/or physical conditions of subjects, this might be directly or indirectly revealed by the patient. Importantly though, researchers will be fully blinded during data analysis. Following informed consent, all subjects will receive a study ID and all the measurements will be stored according to this study ID. As such, data analysis will be blinded between and within groups.

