## **19. DATA MANAGEMENT**

Logbook of all visits and test results will be kept. These are marked only with the research subjects' unique study number. Clinical examinations are entered into the patient record (TakeCare) where it is clearly stated that the tests were performed for research purposes.

All data is saved electronically via RedCap, which is an authentication protected and approved system for research documentation at Karolinska Institutet. All data that is collected is saved with the study ID of the research subjects as a label (sequential number). Names and personal details are not disclosed. Only involved researchers have access to data material. The code list to identify the research subjects is saved as a password-protected document with a paper copy saved in a study folder locked with the responsible researcher. The responsible researcher is responsible for all documents being archived in accordance with KI's rules for research documentation and archiving of research data (saved for at least 10 years).

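### The EMG myopathic class rests on a physician's visual call with no stated masked reading, so imperfect masking could bias the exploratory comparison of patients and controls

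*Combined protocol and SAP*

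**What the plan says.** **How a muscle is classed (Section 12, Electromyography).** Six muscles are examined: "Needle-EMG of deltoid, biceps brachii, trapezius, anterior tibial, vastus medialis, and adductor magnus muscles". At least 20 MUPs are sampled, and mean duration, amplitude and percentage of polyphasic MUPs are recorded. The call itself is visual: "Physician will then assess the EMG results qualitatively by visually observing clear overrepresentation of MUPs with myopathic morphology". It has an anchor, "if more than 50% of the saved MUPs data exhibited myopathic changes", and is taken "together with supportive measures from the qEMG, particularly polyphasia, to classify a muscle as myopathic or not". The text gives no limits for short, small or polyphasic, and none for the qEMG support.

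**How a participant is classed.** The overall EMG result is "classified as definitively myopathic if seen in at least 2 muscles, borderline if seen in one, neurogenic, mixed, or normal EMG findings".

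**Masking (Section 17).** Staff who run the clinical tests, physicians included, are meant not to know the group. The section then allows that "in some cases given the symptoms and/or physical conditions of subjects, this might be directly or indirectly revealed by the patient". Full blinding is promised only at data analysis, by study ID.

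**Comparison with echocardiography (Section 12).** There the plan adds a separate step: "Subsequently, another blinded observer will quantify cardiac chamber dimensions and volumes". No such step is stated for EMG.

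**Analysis.** Section 20 compares categorical characterization variables by a two-tailed chi-square test at P < 0.05. Section 18 calls the physiological comparison with controls exploratory.

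**The concern.** A reader who knows or guesses that a participant is a patient may call doubtful MUPs myopathic more readily. The missing cut-offs leave room for this, because each MUP, and the weight given to qEMG, is still judged. Once the class is recorded, an analyst who sees only study IDs compares biased labels without knowing it.

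Muscle weakness is among the complaints that motivate the study (Section 6a), and Section 6b hopes the results will help decide which tests to use in the clinic and help rule out differential diagnoses. A spurious excess of myopathic EMGs in patients would feed into that use. The primary outcome, change in fatigue at 48 hours, does not involve EMG.

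**Working it through.** The plan states no EMG rate, effect size, power or reader agreement, so it has no figure of its own to reproduce. The check asks how often the planned test would be falsely significant if reading bias were the only difference between the groups.

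**Inputs from the documents**
- Muscles per participant: 6 (Section 12).
- Classes: none called = normal, one = borderline, two or more = definitively myopathic (Section 12). The neurogenic and mixed classes are left out of the model.
- Test: two-sided chi-square, alpha 0.05 (Section 20).
- Group size: 40 in the Synopsis, 30 in Section 9, at least 28 in Section 14. Results are shown for 30 and 40.

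**Assumptions (not in the documents)**
- No true group difference.
- Muscle calls independent within a participant.
- Per-muscle myopathic call rate q of 5% in controls and masked patients, and 10% in unmasked patients.
- Share of patients unmasked: all, half or a quarter. Section 17 says only that it may happen in some cases.

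**Step 1: class probabilities.** P(none) = (1−q)^6; P(one) = 6q(1−q)^5; P(two or more) = 1 − P(none) − P(one).
- q = 5%: 0.95^6 = 73.5%; 6 × 0.05 × 0.95^5 = 23.2%; remainder 3.3%.
- q = 10%: 0.90^6 = 53.1%; 6 × 0.10 × 0.90^5 = 35.4%; remainder 11.4%.

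**Step 2: patient group as a mixture.** With share s unmasked, P(two or more) = (1−s) × 3.3% + s × 11.4%. This gives 11.4% for s = 1, 7.4% for s = 0.5 and 5.3% for s = 0.25. The other classes are mixed in the same way.

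**Step 3: false significance.** The probability of P < 0.05 in the 2 × 3 table was summed over all possible tables, dropping a class that is empty in both groups.

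| Patients unmasked | n = 30 per group | n = 40 per group |
|---|---|---|
| None (no bias) | 3.5% | 3.6% |
| A quarter | 5.0% | 5.8% |
| Half | 9.6% | 12.8% |
| All | 30% | 42% |

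**Step 4: sensitivity**
- Smaller bias: 5% to 7% per muscle with all patients unmasked gives 8% (n = 30) to 10% (n = 40).
- Higher base rate: 10% to 15% per muscle with all unmasked gives 21% to 28%.
- Correlated calls: with a within-person correlation of 0.1 to 0.3, the 5% to 10% case with all unmasked falls to roughly 17% to 25% at n = 30 and 24% to 33% at n = 40. With half unmasked and a correlation of 0.3 it is about 7% to 10%.
- Two classes only (definitively myopathic or not), 5% to 10%, all unmasked: 22% to 31%.

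**The case against.** The case for leaving the plan alone has four parts.

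1. **The call is not free judgement.** It has a 50% anchor on saved MUPs, and qEMG is part of the classification. This stands: discretion is limited. It is not removed, because the features being counted and the qEMG support have no numeric limits.
2. **Masking of physicians is planned.** Section 17 describes failure in some cases only, so the figures for full unmasking are an upper bound and not an expectation. This stands, and with a quarter unmasked the error rate is close to nominal.
3. **The bias modelled is not small.** It doubles the call rate per muscle, and a 2-point rise does little. This stands.
4. **The comparison is exploratory.** This stands and limits the consequences.

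A reader might also infer more than the text supports:
- That the reader is the physician who examined the participant. Section 12 says only that a physician assesses the results.
- That the reader learns the group from the hospital record. Section 19 says examinations are entered there, not that the reader consults it.
- That the two-muscle rule amplifies bias. It does so as a ratio (3.3% to 11.4%), but the absolute gap shrinks to 8.1 points, against 20.4 points for any myopathic muscle (26.5% to 46.9%).
- That bias can run only towards more calls in patients. This is plausible, but nothing in the documents shows it.

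What remains is that the masking of the EMG reading depends on a general plan that admits failure, analysis-stage blinding comes too late to correct it, and a known safeguard used for echocardiography is not stated for EMG.

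**Conclusion.** The point holds as an avoidable risk of bias in an exploratory outcome. The documents do not show that a false finding of myopathy is likely. That would need most or all patients unmasked together with a large shift in reading. Under the assumed rise from 5% to 10% per muscle, false significance runs from near nominal (5% to 6%, a quarter unmasked) through 10% to 13% (half) to 30% to 42% (all). With a 2-point rise it is at most about 10% in the cases examined. The figures rest on assumed call rates, an unknown share unmasked and independent muscle calls; correlation lowers the upper end. The primary conclusion is not affected. The change is worth making because the material needed for a coded reading is already collected.

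**What to change.** In Section 12 (Electromyography), for the research comparison:

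- The existing physician assigns the myopathic or not-myopathic call for each muscle from the saved MUPs and recorded qEMG values, under a shuffled code that is not the sequential study ID, in batches that mix both groups.
- The two-muscle and one-muscle classes are derived from those coded calls.
- The group comparison of recorded duration, amplitude and percentage of polyphasic MUPs is reported alongside the class.
- The text states what stays outside the coded reading: the choice of which MUPs to save, spontaneous activity and the interference pattern. Saved MUPs alone cannot settle the neurogenic and mixed classes, so the coded reading covers only the myopathic call.

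Clinical findings continue to be entered in the record and acted on as Sections 22 and 30 provide; nothing is held back for the coded reading.

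The cost is protocol wording, re-labelling of saved files and some extra reading time for the same physician. No new reader, procedure or visit is needed, and the reading can still be done if classes have already been assigned.

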#### Blood sampling and muscle biopsies

Routine haemoglobin concentration, glucose, lactate, triglyceride and cholesterol levels, leukocyte count, transferrin saturation, and CRP will be determined. Absolute immune cell counts will be determined using BD TruCount, peripheral blood mononuclear cells (PBMCs) will be analysed for distribution of B cells, NK

cells, monocytes, CD4+ T cells, CD8+ T cells, with additional panels to capture plasma, effector and memory cells. Exploratory metabolomic and cytokine profiling will be performed using the Olink PEA platform and GC-MS at the Swedish Metabolomics Center in Umeå, targeted analysis will include IL-6, TNF $\alpha$  and IFN $\gamma$  profiling. Immune results will be correlated with physiological outcomes and exercise response. Muscle biopsy will be also taken from the vastus lateralis muscle under local anesthesia using the Bergström needle technique. Since post-COVID-19 syndrome is associated with mitochondrial fragmentation and reduced levels of metabolites consistent with a hypometabolic syndrome, we will perform these measurements along with histochemical analyzes of fiber size, fiber type, myonuclear content, and gene/protein expression of markers involved in energy processes, muscle atrophy, endothelial dys(function), angiogenesis and mitochondrial biogenesis.

Muscle biopsy: Tissue samples of the vastus lateralis muscle will be obtained under local anaesthesia using the percutaneous Bergström technique from the right leg, after an overnight fast and with no prior exercise during the past 48h. All muscle samples (~200 mg) will be immediately dissected free of any visible fat, excess blood and connective tissue, and then quickly frozen in liquid nitrogen. Samples were stored at -80°C until the analyses.

### **13. PARTICIPANT TIMELINE**

The study will start in September 2022.

Data analysis of the primary outcome and first manuscript is expected to be submitted by December 2023.

Further blood and tissue analysis from the physiological characterization and exercise sessions (i.e., muscle biopsies, blood sample cytokine profile, PBMCs) is estimated to be completed by September 2024.

The 1-year follow-ups are expected to finish during Summer 2024 and the study completion is estimated to be completed in December 2024, including data analysis and manuscripts.

Participant timeline, including details of the visits/interventions is shown in Figure 1. Briefly, we estimated that participants will be enrolled in the study for approximately 1 year from the first baseline visit to the last follow-up visit.

### **14. SAMPLE SIZE**

Determining an appropriate sample size for this study was challenging as the post-COVID-19 syndrome was new and there was no established data on the expected effect size of the interventions and the consistency of patient responses. Nevertheless, based on clinical observations from previous studies, we expected a markedly different response to exercise in patients compared to controls. Indeed, symptom variability after acute exercise in myalgic encephalomyelitis/chronic fatigue syndrome (ME/CFS) shows moderate to large effect sizes for most symptoms assessed with VAS scales. Our a priori estimate (using G\*Power) was that we would need at least 28 patients and 28 controls to detect a moderate effect size (Critical F 0.25) between groups in a within-between interaction design with a power of 80% and an alpha of 5%.

### **15. RECRUITMENT**

Patient inclusion is ensured through collaboration with the post-COVID-19 clinic and coordinator for research on this patient group established at Karolinska University Hospital. Patients will be informed about the current study and the opportunity to participate. Other social channels, including patients' post-COVID-19 association in Sweden will be sought if needed.

### **16. ALLOCATION**

The research team will randomly allocate the order of exercise interventions. Same allocation will be applied in both groups. Research Electronic Data Capture (Redcap) software will be used for the random allocation. In addition, exercise order will be recorded and incorporated into the statistical model.

## **17. BLINDING**

Researchers will be blinded as far as possible during data collection, in terms of group (post-COVID-19 vs. control). For example, the study personnel who conduct the clinical tests and/or exercise trials (physicians, biomedical analyst, research assistants etc.) will not be aware of the group allocation (Patient or Control). However, in some cases given the symptoms and/or physical conditions of subjects, this might be directly or indirectly revealed by the patient. Importantly though, researchers will be fully blinded during data analysis. Following informed consent, all subjects will receive a study ID and all the measurements will be stored according to this study ID. As such, data analysis will be blinded between and within groups.

## **18. DATA COLLECTION**

At baseline and at 1-year follow-up, all physiological variables will be assessed under strictly standardized procedures in a laboratory setting. Physiological functions of the patients with post-COVID-19 condition will be compared with a well-matched healthy control group in an exploratory manner, as this patient population has yet to be characterized. Measurements before and after 1 year will be compared to determine if improvements are more related to certain physiological factors than others. Figure 1 and section 12 provide details in regards to the data collection for each particular outcome.

## **19. DATA MANAGEMENT**

Logbook of all visits and test results will be kept. These are marked only with the research subjects' unique study number. Clinical examinations are entered into the patient record (TakeCare) where it is clearly stated that the tests were performed for research purposes.

All data is saved electronically via RedCap, which is an authentication protected and approved system for research documentation at Karolinska Institutet. All data that is collected is saved with the study ID of the research subjects as a label (sequential number). Names and personal details are not disclosed. Only involved researchers have access to data material. The code list to identify the research subjects is saved as a password-protected document with a paper copy saved in a study folder locked with the responsible researcher. The responsible researcher is responsible for all documents being archived in accordance with KI's rules for research documentation and archiving of research data (saved for at least 10 years).

## **20. STATISTICAL METHODS**

Analyses will be performed using IBM SPSS Statistics for Windows, version 29.0 (Armonk, NY: IBM Corp). To assess the primary outcome (post-exertional symptom exacerbation from baseline to 48h after each exercise), a mix-linear model was initially planned to analyse the differences in symptom changes following three exercise sessions (HIIT, MICT, ST), between the two groups (post-COVID-19 patients vs. control). Subject ID and the order of exercise sessions will be used as random effect in the mix-linear model. Pairwise comparisons will be performed when significant main or interaction effects are detected, using Bonferroni correction.

However, during data analysis, the aforementioned statistical plan was amended given the nature of the data (not normally distributed data). Particularly, a significant number of the control subjects responded “zero” change in the visual analog scale assessing the symptom exacerbation. As such, non-parametric tests (Mann-Whitney test, Kruskal-Wallis test) were used to compare differences in symptoms following exercise trials between the groups.

A mixed-linear model was used to analyze differences in continuous data (CPET variables, interleukin (IL)-6, Creatine Kinase) following three exercise sessions (HIIT, MICT, ST) between the two groups (post-COVID-19 patients vs. control). Subject ID and order of exercise sessions were used as random effect in the mix-linear model. Pairwise comparisons will be performed when significant main or interaction effects are detected, using Bonferroni correction.

For the physiological characterization assessments, two-tailed Chi-square test or Student t-test will be used to examine differences in categorical or continuous variables, respectively, between the post-COVID-19 patients and the control group.

Results will be presented as mean (SD), and significance will be set at  $P < 0.05$ .

Missing data will be treated as missing values in the statistical models, unless otherwise specified. In retrospect, there was no need for missing data imputation. Therefore, missing data were treated as missing values.

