| SCHEDULE           | 
Recruiting first participant: September 2022
 
Recruiting last participant: July 2023
 
Study planned completion: July 2024
                                                                                                                                                                                                                                                                                                                                                      |

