## **7. OBJECTIVES**

### **7a. Primary objective and hypothesis**

Post-exertional malaise (PEM) symptoms of post-COVID-19 subjects and age/sex matched controls in response to three different exercise trials. The primary outcome is the comparison of the change in fatigue rating using the visual analog scale (VAS) 0-10 before and 48h after each training trial between the post-COVID-19 group and the control group. We hypothesize that the post-COVID-19 group will suffer from persistent fatigue at 48h after exercise compared to baseline, whereas control group will return to the baseline level at this time point.

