## **25.PROTOCOL AMENDMENTS**

Amendments have been approved by the Swedish Ethical Authority REF: 2022-02999-02. This study is registered in [ClinicalTrials.gov](https://clinicaltrials.gov/ct2/show/study/NCT05445830) NCT05445830.

The study has registered and begun following the ethical approval of the version 1.1 amendments.

The statistical plan was revised during the data analysis (Aug 2023), given that the primary outcome (post-exercise symptom exacerbation via visual analog scale) required a different statistical approach (see above).

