| Introduction Background and objectives                       | 2a       | Scientific background and explanation of rationale                                                                                                                                          | 4                    |
|                                                              | 2b       | Specific objectives or hypotheses                                                                                                                                                           | 4, S12               |
| Methods Trial design                                         | 3a       | Description of trial design (such as parallel, factorial) including allocation ratio                                                                                                        | 5                    |
|                                                              | 3b       | Important changes to methods after trial commencement (such as eligibility criteria), with reasons                                                                                          | NA                   |
| Participants                                                 | 4a       | Eligibility criteria for participants                                                                                                                                                       | 4-5                  |
|                                                              | 4b       | Settings and locations where the data were collected                                                                                                                                        | 4-5                  |
| Interventions                                                | 5        | The interventions for each group with sufficient details to allow replication, including how and when they were actually administered                                                       | S16-22               |
| Outcomes                                                     | 6a       | Completely defined prespecified primary and secondary outcome measures, including how and when they were assessed                                                                           | 5, S12               |

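### The primary test was chosen during analysis from how the control group answered, against a promise of blinded analysis, and nothing commits the authors to reporting the planned model

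*Combined protocol and SAP*

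**What the plan says.** Section 7a defines the endpoint: "The primary outcome is the comparison of the change in fatigue rating using the visual analog scale (VAS) 0-10", before and 48 h after each session, patients against controls. Section 20 states that "a mix-linear model was initially planned to analyse the differences in symptom changes following three exercise sessions (HIIT, MICT, ST"), between the two groups, with subject and session order as random effects and Bonferroni-corrected pairwise comparisons. Section 16 also promises that order will enter the statistical model, and Section 14 bases the sample size on a within-between interaction.

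Section 20 then says that "during data analysis, the aforementioned statistical plan was amended given the nature of the data (not normally distributed data"). The particular reason is that "a significant number of the control subjects responded" with zero change on the VAS. Mann-Whitney and Kruskal-Wallis tests replaced the model for symptoms; the mixed model was kept for CPET variables, IL-6 and creatine kinase.

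Section 25 confirms the timing: "The statistical plan was revised during the data analysis (Aug 2023"). The synopsis schedule has "Recruiting last participant: July 2023". Section 17 says that "researchers will be fully blinded during data analysis" and extends this to comparisons between groups and within them. In the CONSORT checklist, item 3b, "Important changes to methods after trial commencement (such as eligibility criteria), with reasons", is marked NA.

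**The concern.** A primary test should be fixed before anyone sees outcomes split by group. Here the stated trigger is a feature of one group's outcomes. Once the test depends on the data in this way, its nominal 5% level is no longer guaranteed. A reader also cannot tell whether the choice affected the answer unless the planned analysis is shown beside it.

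The replacement raises problems of its own. It changes what is estimated, drops parts of the design that other sections rely on, and is described too loosely to be reproduced.

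**Working it through.** **1. The sections side by side.** Section 17 promises analysis blinded between groups. Section 20 gives a reason for changing the primary test that needs outcomes sorted by group. Even if the groups carried neutral codes, the outcomes had been split by group when the test was chosen. Section 25 places this one month after the planned end of recruitment. Section 3 lists versions 1.0 and 1.1, both dated 2022, and the ethics reference in Section 25 is that of version 1.1, so no listed version covers the August 2023 change. Item 3b of the checklist (NA) contradicts Section 25.

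**2. What the switch removes.** The rank tests, as described, carry no subject effect, no group-by-session interaction (the basis of the sample size in Section 14) and no order term (promised in Section 16). Section 20 does not say whether they are run per session, on subject means or on all records pooled, which one is primary, or whether Bonferroni still applies.

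**3. Is the stated reason sufficient?** A mixed model assumes roughly normal residuals and random effects, not normal raw scores. The group contrast is a difference of averages over about 30 people per group (Section 9; the synopsis says 40). Many zeros in one group mainly signal unequal spread, which robust or resampling inference can handle without giving up the planned estimand.

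**4. Size.** The documents give no results, SDs, zero shares or within-person correlation, so all inputs below are assumed. With 3000 runs per setting, the Monte Carlo standard error near 5% is √(0.05 × 0.95 / 3000) = 0.004. For balanced data the mixed-model group effect is represented by a t-test on each person's mean over three sessions.

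*Setting A: both groups have the same distribution.* 28, 30 or 40 per group; rounded changes with latent SD 1.5; 30% or 60% set to zero; latent correlation 0.3-0.7.

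| Procedure at nominal 0.05 | Rejection rate |
|---|---|
| Planned-type group effect | 0.047-0.058 |
| Mann-Whitney on subject means | 0.046-0.058 |
| Smaller P of these two | 0.063-0.074 |
| Any of three session Mann-Whitney tests, uncorrected | 0.12-0.14 |
| The same at 0.05/3 = 0.0167 | 0.037-0.051 |
| One rank test on all records pooled | 0.08-0.18 |

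For three independent tests the figure would be 1 − (1 − 0.05)³ = 0.143.

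*Setting B: no mean worsening, but unequal spread.* 30 per group; controls 50-85% zeros, otherwise +1 or −1; patients symmetric about zero with SD 1.5-2.5; correlation 0.5.

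| Procedure at nominal 0.05 | Rejection rate |
|---|---|
| Mann-Whitney, one session | about 6-10% |
| Welch t-test, one session | about 5% |
| Group contrast on subject means | about 5% |
| Any of three session Mann-Whitney tests, uncorrected | about 16-24% |

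Bonferroni deals with the three sessions but not with the excess due to unequal spread.

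**5. Can the choice change the answer?** With a true difference (28, 30 or 40 per group; patients shifted by 0.5-1.0 points; 20% zeros against 60%; correlation 0.5), the planned-type test and Mann-Whitney, both on subject means, disagreed on significance in about 2-13% of runs.

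**The case against.** The strongest reply has four parts.

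- **The change is disclosed.** Sections 20 and 25 give the reason and Section 25 the date. Nothing suggests that significance drove it. This stands.
- **Unblinding is not proved.** A reader might infer that the analysts knew who was a patient. The documents do not say who made the change or whether groups were coded, and the word control could have been added when the text was written. So unblinding is a strong inference, not a stated fact. The conflict with Section 17 remains, because the outcomes were examined by group either way.
- **Rank tests are conventional for a bounded score with many zeros.** This is fair as far as it goes. Mann-Whitney also tests a different null from equal means. But in setting B a patient is as likely to score above a control as below, so a rejection would still be misread as exacerbation. That excess would arise even with a prespecified Mann-Whitney test; it measures the test's sensitivity to spread, not the harm of switching.
- **The prespecified result may not be lost.** No section says that the mixed model was not run or will not be shown, and it can still be fitted. Nor do the documents contain a primary P value that could be called wrong. What is missing is a commitment to report the model.

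A reader might also infer a large loss of power. Like for like there is almost none: at 30 per group and a 0.75-point shift, both subject-mean tests had power of about 0.71.

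**Conclusion.** The point holds. By the plan's own account, the primary test was replaced during analysis for a reason drawn from one group's outcomes. This conflicts with Section 17, and reporting of the planned model is not assured. The inflation from the swap alone is modest, about 6-7% against 5%, if both candidates are well-defined subject-level tests. The greater risk lies in the undefined replacement: about 12-14% for three uncorrected session tests when the groups are identical, about 16-24% when only the spread differs, and 8-18% for a pooled rank test.

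These ranges depend on assumed zero shares, SDs and correlations. They illustrate multiplicity, ignored clustering and unequal spread; they do not estimate the error in this trial. The conflict between Sections 17 and 20 and the missing reporting commitment rest on the text alone. The checklist entry by itself would be clerical.

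**What to change.** 1. Report the originally planned mixed model (group, session, order, subject) as the prespecified primary result, with a heteroscedasticity-robust, bootstrap or permutation P value and confidence interval for the group contrast.
2. Label the rank tests as post hoc sensitivity analyses. State whether they are per session or on subject means, and apply Bonferroni across sessions.
3. State in Section 17 the actual blinding status when the plan was changed: who made the change, and whether groups were coded.
4. Replace NA at checklist item 3b with the change, its date and its reason.

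The cost is one extra model on existing data, some wording, and probably a less favourable blinding statement.
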